### 1.2 The challenges faced by Community Learning Centres (CLCs)

Among the major challenges encountered by CLCs are lack of certification and access to public examinations, high turnover of teachers and minimal compensation, security and safety issues faced by the students and teachers in and out of school, and lack of data on out of school children. Most CLCs are severely underfunded, rely on UNHCR for teacher compensation, are overcrowded, lack proper classrooms, do not have sufficiently trained teachers, and students often lack exposure to sports or other recreational activities integral for childhood development [2]. Many CLCs use the Malaysian national syllabus; yet, there is no formal certification of learning by any authority because the lack of state recognised documents deters refugee students from sitting for examinations and obtaining education level certifications. Additionally, CLCs are considered ‘irregular’ as they are unable to obtain official registration as educational institutions. As such, CLS are subject to closure at any time by the authorities, bringing about an instability for the CLCs and continued education for the children.

Published literature reveals that a major problem in refugee schools in Malaysia was high absenteeism and dropping out of school, besides bullying, and lack of cooperation between school staff and parents among others [3]. The above findings concur with previous findings of UNICEF which also attributes the high absenteeism and dropping out of school by refugee children to the pressure to work and support families, especially for adolescents, the inability of families to afford education, and living in remote areas [2]. Another study conducted in a refugee school revealed that the students in the study experienced socio-emotional difficulties and their teachers experienced stress [4], while yet another study on sexual health knowledge with school age Chin and Kachin children revealed low levels of knowledge about their body and safe sex [5]. In the latter study, almost a fifth of the children, mostly boys, reported inappropriate sexual contact. About three out of four children stated that they did not know where to go for help if someone forced physical intimacy on them [5].

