#### Component 3: The SEL-PLA for the students (implemented by the teachers)

The third component, PLA for the students involves teachers’ implementation of PLA to their students’ 15 interactive workshops. These workshops within a child-focused, age-appropriate framework are meant to facilitate and help students be aware, absorb, reflect and practice SEL principles. These sessions are planned to begin after at least 7 months of teacher training sessions.

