### 2.6 Participants

#### 2.6.1 Sample

**Participants are from a community learning centre (CLC).** The CLC involved in this programme is located in urban settings in Kuala Lumpur, the capital city of Malaysia. Established in March 2007, the centre was set up to provide education for the children from Myanmar refugee families. Classes ranged from pre-school to secondary school. In the year 2021, there were 16 teachers and 215 students enrolled for the academic year.

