#### 2.6.3 The students and parents

All students aged 6 to 19 still enrolled in the academic year of 2022 will be invited to participate. Students who are willing to provide assent and whose parents or caregivers are willing to provide informed consent will be enrolled into the evaluation. We are aware that there may only be a small number of students that will be part of the collected data at this early stage and also the limited timeframe to observe the effects of the intervention. We intend to plan a full-scale randomised trial once we have as a follow up to this study; hence, there were no power calculations of sample size at this stage. Nevertheless, for a study with an effect size of 0.3 (as per studies in the literature) [15] and a power of 80%, a sample size of at least 90 students would be needed to test the association at 5% levels using two tailed test.

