#### 2.7.2 Secondary outcomes (Effects)

*Student resilience*, *academic performance*, *SEL competencies*, *mental health status*. Resilience will be measured using the Child Resilience Questionnaire, a multi-domain measure of resilience developed by The Childhood Resilience Study [43]. This scale measures five domains of individual (self) and environmental (school and friends, family, and culture) components associated with resilience.

Academic achievement will be assessed using the Academic Performance subsection scores from the teacher report of the Social Skills Improvement System Rating Scales (SSIS) [44]. SSIS is a scale that measures Social Skills, Problem Behaviours and Academic Competence. The average grade point of each student will also be obtained from their school records.

SEL competencies will be measured using pre/post-tests to be administered after SEL-PLA activities are implemented, supplemented by the SSIS [44] subsections in Social Skills, collected from students, teachers and parents.

Mental health of the students will be assessed using the Strengths and Difficulties Questionnaire [45,46], which is a screening tool for psychological adjustment in children and aims to detect emotional or behavioural problems. Data will be collected from teachers, students and parents.

In addition, focus group discussions with teachers will also be used to elicit observed differences in their students before, during and after the implementation of the SEL-PLA activities. Given the limited time teachers have to implement the student SEL-PLA (due to COVID-19 restrictions and lockdowns), quantitative effects may not be immediately measurable. Hence, qualitative observations of the effects of the SEL activities will be elicited from focus group discussions with the teachers as well.

*Teacher mental health status and SEL competencies*. Mental Health will be measured using the Depression Anxiety and Stress Scale, 21-item version (DASS-21) [47]. DASS-21 has three subscales that measures depression, anxiety and stress symptoms in an individual.

Teaching competencies for SEL will be measured using pre-post assessments to be administered at every teacher training session. Focus group discussions with teachers will held at intervals of the study to elicit on their perception of their own SEL competencies, areas to improve on and their confidence in providing a supportive SEL environment for their students.

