### 2.8 Data analysis

#### 2.8.1 Quantitative data

For all quantitative data, descriptive statistics will be run with continuous variables summarized using means and standard deviations and categorical variables summarized using frequencies and proportions.

The assessment of intervention implementation will be using the summary measures collected from observations and self-reports.

For the assessment of impact, we will analyse scores from the respective instruments to estimate if there are differences before and after the intervention using T-test, Wilcoxon rank sum test, one-way repeated measures ANOVA or the Friedman Test, depending on whether the data obtained fulfilled the assumptions required for the different type of analyses.

Further, path analysis will be used to test for mediators and moderators of SEL competencies and the relationship with resilience and academic performance in students.

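### The four before-after tests named for the student outcomes ignore that students share about 16 teachers, so a paired test is too optimistic if change correlates within class

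*Protocol article*

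**What the plan says.** Section 2.8.1 estimates before-after differences in the instrument scores "using T-test, Wilcoxon rank sum test, one-way repeated measures ANOVA or the Friedman Test, depending on whether the data obtained fulfilled the assumptions required". It adds that "path analysis will be used to test for mediators and moderators of SEL competencies", without naming an estimator. No class or teacher term appears in either statement.

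On the structure of the data, section 2.6.1 reports that "there were 16 teachers and 215 students enrolled for the academic year" (2021). Component 3 of the intervention is headed "The SEL-PLA for the students (implemented by the teachers)", and its text has teachers running the workshops with their own students. On ratings, Table 1 lists teachers, students and parents as sources for resilience, social skills and mental health. Section 2.7.2 says of the mental health measure: "Data will be collected from teachers, students and parents". The SSIS academic scale in that section comes from the teacher report alone.

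On sample size, section 2.6.3 disclaims a formal power calculation but still states that, at an effect size of 0.3 and 80% power, "a sample size of at least 90 students would be needed to test the association at 5% levels using two tailed test". On retention, section 1.2 says that "a major problem in refugee schools in Malaysia was high absenteeism and dropping out of school".

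**The concern.** Each of the four tests treats students as independent of one another. The protocol's own theory says otherwise. Section 2.3 describes teachers as driving the programme and has their capacity pass through to their students. If that happens, students of one teacher change together, and the student count overstates the information in the data. The choice among the tests turns on whether assumptions are met, but if independence fails there is no valid option on the list. An analysis plan that followed this section would inherit the problem, so this is more than detail left for later.

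At stake is the precision claimed for student change in resilience, social skills, mental health and academic performance. The Discussion says the data will feed the design of a cluster randomised trial. An understated error could make an uninformative change look established, and these tests give no estimate of between-class variation, which that design needs.

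A second, smaller matter is that three of the four tests, in their paired form, use only students with every required score, in a setting described as prone to absence and drop-out.

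**Working it through.** **Inputs from the protocol article.** 16 teachers and 215 students (2.6.1); effect size 0.3, 80% power, two-sided 5%, at least 90 students (2.6.3).

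**Inputs assumed, because the documents give none.** Change-score ICC of 0.01 to 0.20; one class per teacher; drop-out of 10 to 40%; pre-post correlation r of 0.3 to 0.7.

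**1. The plan's own figure.** For a paired test of a standardised change, n = ((1.960 + 0.842)/0.3)² = 87.2, so 88. The exact paired t calculation gives 90, with power 80.4%. A correlation of 0.3 would need 85, and two independent means 175 per group. So 90 reproduces as a paired test on independent students with complete pairs, with no allowance for clustering or drop-out.

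**2. Clustering.** With m = N/16 students per class, the design effect is DE = 1 + (m − 1) × ICC. The true standard error is √DE times the naive one. The actual two-sided alpha of a naive paired test is 2 × (1 − Φ(1.96/√DE)).

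| N | m | ICC | DE | √DE | Actual alpha | Power, corrected test |
|---|---|---|---|---|---|---|
| 90 | 5.6 | 0.01 | 1.05 | 1.02 | 5.5% | 80% |
| 90 | 5.6 | 0.05 | 1.23 | 1.11 | 7.7% | 73% |
| 90 | 5.6 | 0.10 | 1.46 | 1.21 | 10.5% | 65% |
| 90 | 5.6 | 0.20 | 1.93 | 1.39 | 15.8% | 54% |
| 215 | 13.4 | 0.01 | 1.12 | 1.06 | 6.5% | 99% |
| 215 | 13.4 | 0.05 | 1.62 | 1.27 | 12.4% | 93% |
| 215 | 13.4 | 0.10 | 2.24 | 1.50 | 19.1% | 84% |
| 215 | 13.4 | 0.20 | 3.49 | 1.87 | 29.4% | 65% |

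A simulation of a naive one-sample t-test on clustered change scores agrees at ICC 0.05, 0.10 and 0.20: 7.6%, 10.2% and 16.0% with 90 students, and 12.0%, 19.3% and 30.1% with 215. A t-test on the 16 class mean changes held 4.6 to 5.2%. Enrolling more students under the same teachers raises power but makes the naive test's alpha worse.

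**3. The rank sum test.** As named, it compares two independent samples. On before-after scores from the same students it ignores r. Before clustering, its actual alpha is about 2 × (1 − Φ(1.96/√(1 − r))), which is 1.9%, 0.6% and 0.03% at r = 0.3, 0.5 and 0.7. It is therefore conservative. With clustering the variance ratio becomes (1 − r) × DE. At r = 0.5 and DE = 2.24 this is 1.12, and alpha is about 6.4%. The two errors pull in opposite directions and would cancel only by chance.

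**4. Complete records.** With 10, 20, 30 or 40% drop-out, 90 enrolled students leave 81, 72, 63 or 54 complete pairs. Power for the paired t-test, before clustering, is then 76%, 71%, 65% or 58%. Retaining 90 pairs would need 100, 113, 129 or 150 enrolled.

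**The case against.** The strongest objection is that none of this touches the primary question. Feasibility is judged by teacher interviews and by 70% thresholds for participation, fidelity and dosage (2.7.1), which use none of these tests. Effects are secondary, section 2.7.2 concedes that they may not be measurable in the time available, and in a single-arm study even a correct p-value would not establish an effect. This stands, and it lowers the severity.

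The size is also assumed. At an ICC of 0.01 with 90 students the inflation is negligible. One class per teacher is not stated. The 215 is 2021 enrolment, whereas consenting students aged 6 to 19 enrolled in 2022 are invited. Teachers are one of three rating sources on most scales, and a stable rating habit largely cancels in a change score by the same rater. These points stand too. What remains is shared delivery, any shift in a teacher's rating, and the academic scale, which only teachers complete.

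Three stronger readings are tempting but not supported:

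- **Every planned test needs complete records.** The rank sum test as named does not, an unpaired t-test would not, and the path analysis has no stated missing-data method.
- **Standard errors are too small throughout.** That requires a positive ICC of change. The rank sum test errs the other way before clustering, and student nesting does not apply to teacher outcomes.
- **The students who stay are better adjusted.** Section 1.2 describes refugee schools generally, gives no rate, and attributes absence and drop-out to work pressure, cost and remoteness.

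The rules for missing data may sit in an analysis plan or full protocol that is not shown, and so may the number of student timepoints, which is in a figure that is not shown. The complete-records limb is therefore secondary.

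**Conclusion.** The concern holds for the secondary student outcomes. All four named tests assume independent students, the design gives good reason to expect correlation within a teacher's class, and the assumption check cannot resolve it. At assumed ICCs of 0.05 to 0.10, a naive paired standard error is about 10 to 17% too small with 90 students and 22 to 33% too small with 215 (1 − 1/√DE). The nominal 5% test then runs at about 8 to 10% and 12 to 19% respectively. At 0.01 the effect is slight; at 0.20 it reaches about 16% and 30%. All of this rests on a positive ICC and one class per teacher.

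Two lesser points go with it. The paired t-test, repeated measures ANOVA and Friedman test discard students with incomplete scores. The rank sum test is the wrong test for before-after data from the same students. Severity is moderate: it should be corrected before the effect analysis, but it does not affect the feasibility conclusions.

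**What to change.** Record a class or teacher identifier for each student. Analyse student change with a linear mixed model: time as a fixed effect, random effects for student and class including class-by-time, a small-sample correction for about 16 classes, and all available observations. A simpler alternative is a t-test on the class mean changes.

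If a nonparametric test is kept, name the Wilcoxon signed-rank test in place of the rank sum test, and apply it to class-level changes.

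Report the change with its 95% confidence interval, the class ICC and student retention. The last two serve the planned cluster randomised trial directly. State how students with more than one teacher are assigned to a class.

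The cost is one extra variable, a few sentences in the analysis section, and somewhat wider confidence intervals.

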### 2.4 Study design

A pre-post single arm design combined with qualitative and quantitative methods will be used to address the research questions (see Table 1).

**Table 1 pone.0273239.t001:** Methods, data collection instruments and data source according to research questions.

Research Question	Data collection Instruments	Data Source
1. Is PARSEL feasible in the context of CLC in terms of acceptability and implementation, from the perspective of teachers? a. Acceptability b. Implementationi. i. Fidelity ii. Changing needs and support throughout the programme	Focus group discussion (FGD) In depth Interviews Lesson observations Teacher self-report log Focus Group Discussion (FGD) Focus group discussion (FGD) WhatsApp group Reflective open-ended questions and journaling SEL Needs assessment survey Safe, Inclusive, and Respectful Climate survey (School Climate Survey) [39]	Teachers Teachers Programme team Teacher Teacher Teacher Teacher Teacher Teacher Teacher
2. What is the impact of the programme on: a. Student resilience and academic performance b. Student SEL competencies c. Student mental health status d. Teacher mental health status e. Teacher SEL competencies	Child Resilience Questionnaire Student academic grades Social Skills Improvement System Rating Scale (SSIS) [38] Focus group discussion (FGD) SDQ [36] Depression, Anxiety and Stress Scale, 21 items (DASS-21) [37] Pre post tests In depth interviews	Students, Teachers, Parents Teachers Students, Teachers, Parents Teachers Students, teachers, parents Teachers Teachers Teachers
3. Do any of the proposed mechanisms in the conceptual framework explain the link between the programme, resilience and academic achievement? Was the theory of change realised in the study design?	Safe, Inclusive, and Respectful Climate survey (School Climate Survey) [39] Focus group discussion (FGD) Child Resilience Questionnaire Student academic grades Social Skills Improvement System Rating Scale (SSIS) [38]	Teacher Teacher Student, Parent, Teacher Teacher Student, Parent, Teacher

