#### 2.6.2 The teachers

All teachers from the school (at current baseline, n = 16) will be invited to participate. Teachers will be enrolled into the study if they are willing to provide informed consent and agreeable to commit for the full duration of the programme.

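### The before-after test is chosen from the data, score by score, so the hypothesis tested can vary and need not match the mean change; the named rank sum test also ignores the pairing

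*Protocol article*

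**What the plan says.** The study is single-arm with measurements before and after (section 2.4: "A pre-post single arm design combined with qualitative and quantitative methods"), so each person's scores are paired. Section 2.8.1 says the instrument scores will be analysed "to estimate if there are differences before and after the intervention". The candidates are "T-test, Wilcoxon rank sum test, one-way repeated measures ANOVA or the Friedman Test", and the choice is made "depending on whether the data obtained fulfilled the assumptions required for the different type of analyses". No default test, diagnostic or cut-off is given. The same section has "continuous variables summarized using means and standard deviations", with no exception for a score that moves to a rank test.

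Section 2.6.3 says that no power calculation was made at this stage. It then gives an orientation figure for an effect size of 0.3, 80% power and a two-sided 5% level: "a sample size of at least 90 students would be needed". The teacher scores rest on few people (section 2.6.2: "at current baseline, n = 16").

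**The concern.** A t-test on paired scores asks whether the mean change is zero. A rank test asks something else: whether changes are symmetric about zero (signed-rank), or whether one set of scores tends to exceed the other (rank sum). When change scores are symmetric the questions nearly coincide. When they are skewed they part, and skew is one of the things that triggers the switch.

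Three consequences follow. First, the hypothesis for a score is settled by the data rather than by the plan. Second, resilience, social skills and mental health are each reported by students, teachers and parents, so one instrument could be tested for a mean change in one informant and a rank shift in another. That weakens the comparison across sources planned in section 2.8.3. Third, the p-value may not belong to the mean and standard deviation beside it. The discussion says the data will help to design a cluster randomised trial, and that needs a mean change, its standard deviation and an interval.

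Separately, the rank test named for two time points treats the before and after scores as two unrelated groups.

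**Working it through.** **Inputs from the protocol article.** Effect size 0.3, 80% power, two-sided 5%, 90 students (2.6.3); 16 teachers (2.6.2); list of tests and rule for choosing (2.8.1).

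**Inputs assumed, because the document gives none.** Pre-post correlation r = 0.3, 0.5, 0.7; skewness of the change scores 0, 1 or 2; Shapiro-Wilk at 5% on the change scores as the assumption check.

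**Step 1: reproduce the 90.** Paired t-test on change with d = 0.3. Normal approximation: n = ((1.960 + 0.842)/0.3)² = 87.2, so 88. The noncentral t gives 89.15, so 90. Power is 79.9% at 89 and 80.4% at 90. The stated figure matches a paired test of mean change.

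**Step 2: the rank sum test as named, on paired normal data, n = 90, d = 0.3.** With unit variance at each time, the standard deviation of change is √(2(1−r)), so the shift is 0.3√(2(1−r)). The rank sum statistic is scaled as if the two sets were independent. Its mean is therefore about √(3/π) × 0.3 × √(90(1−r)), and its standard deviation about √(1−r) instead of 1. Power ≈ Φ((mean − 1.96)/√(1−r)):

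| r | mean | SD | power, formula | power, simulated | paired t-test |
|---|---|---|---|---|---|
| 0.3 | 2.33 | 0.84 | 67% | about 66% | about 80% |
| 0.5 | 1.97 | 0.71 | 50% | about 49% | about 80% |
| 0.7 | 1.52 | 0.55 | 21% | about 21% | about 80% |

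Repeat simulations differ by up to about 3 points. With no change at all, the rank sum test rejects about 2%, 1% and 0.1% of the time or less, so it is conservative as well as weak.

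**Step 3: if the paired signed-rank test was meant.** True mean change zero; centred gamma with shape 4 (skewness 1), centred exponential (skewness 2) and normal change; switch to signed-rank when Shapiro-Wilk rejects. Simulated rejection rates:

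| n | skewness | t-test fixed in advance | data-chosen test |
|---|---|---|---|
| 90 | 0 (normal) | 5% | 5% |
| 90 | 1 | 5% | about 12% |
| 90 | 2 | 6% | about 35% |
| 16 | 2 | 8-9% | 11% |

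At n = 90 the check fires in about 93% of data sets at skewness 1 and in all at skewness 2, so the switch would be routine. At n = 16 and skewness 2 it fires in roughly 72%, but the two tests then differ little.

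**Step 4: the same skewed-change scenario with the rank sum test.** With a normal baseline, zero mean change, n = 90 and pre-post correlation 0.71 or 0.57, the data-chosen test rejects about 0.4% to 7% of the time. Skew alone is also not enough: if a score is equally skewed before and after, the signed-rank test rejects 4-6% and the rank sum test 0-3%. Larger rank sum rates (8-61% at n = 90) appeared only in an extreme scenario where a score turned from right-skewed to left-skewed with mean and standard deviation unchanged.

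**The case against.** **The inflation figures are not the plan's.** A reader might infer that the plan as written gives 12% to 35% false positives. The document does not support that. It names neither Shapiro-Wilk nor the signed-rank test, and with the test it does name the same scenario gives about 0.4% to 7%. This objection stands: the figures in step 3 hold only under their stated assumptions. What remains for the named test is mainly its loss of power on paired data.

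**A rank rejection is not an error for a broad question.** The plan asks about differences and effects, not about means only. In the exponential example the median change is ln 2 − 1 = −0.31 standard deviations, so most students did shift, and detecting that is legitimate. This also stands, so the step 3 rates are not false positives for every possible question. They show a mismatch with the mean. The point that survives is that the plan does not hold to one question: it describes and sizes by the mean, then lets the data decide whether the mean is tested.

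**The means and standard deviations are general descriptive statistics.** True. The document does not say that a mean change will be printed beside a rank p-value, so calling the p-value unrelated to the reported change would go too far. It need not match; that is all.

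**Detail belongs in an analysis plan.** Which test goes with which score may well be left there. But section 2.8.1 does not stay silent. It states a rule of choosing from the data, and an analysis plan could cure this only by replacing the rule.

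**The stakes are low.** Feasibility is the main focus, the success thresholds (70% participation, fidelity and dosage) do not use these tests, and section 2.7.2 warns that quantitative effects may not be measurable yet. This stands and limits the weight of the point.

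**Conclusion.** The point holds in this form: the test, and with it the hypothesis, is chosen from the data for each score, while the summaries and the only sizing concern the mean; and the rank sum test named does not suit paired data.

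The firmest figure is the power loss. At 90 students and a standardised change of 0.3, power is about 66%, 49% and 21% at correlations of 0.3, 0.5 and 0.7, against 80% for the paired t-test. It assumes normal scores and those correlations. The rejection of a zero mean change in about 12% or 35% of studies is conditional on three assumptions: signed-rank intended, Shapiro-Wilk at 5% as the check, and change scores with skewness 1 or 2. It disappears when change is symmetric. At 16 teachers the choice makes little difference, and there the t-test itself runs at 8-9% under skewness 2.

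The outcomes affected are secondary in a feasibility study. The change should be made, but nothing in the primary evaluation depends on it.

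**What to change.** Replace the conditional rule in section 2.8.1 with one analysis fixed in advance. For every student and teacher score with two time points, report the mean within-person change with its 95% confidence interval from one named paired method. This can be the paired t method, or a bootstrap interval if that is used for all scores; it should not switch on the data. Name the Wilcoxon signed-rank test, not the rank sum test, as a sensitivity analysis. For scores taken more than twice, such as the school climate survey, likewise name one analysis beforehand.

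The cost is a sentence or two and no extra data. The downside is slightly less power than a rank test if change scores are symmetric with heavy tails. At 90 students and an effect of 0.3, power stays at about 80%, the level quoted in section 2.6.3.

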## 2. Methods

### 2.1 Aims and objectives

The aim of the study is to evaluate the feasibility of a complex intervention on social and emotional learning, focused on increasing resilience and academic performance in refugee children in the context of a community learning centre. The study also aims to evaluate the effects of the SEL intervention on students and teachers in the CLC.

Our primary research question is:

Is PARSEL feasible in the context of CLC in terms of acceptability and implementation, from the perspective of teachers?

Our secondary research questions are:

Does PARSEL have any effects in improving resilience and academic performance in refugee students?Do any of the proposed mechanisms in the conceptual framework explain the link between the programme, resilience and academic achievement? (Was the theory of change realised in the study design?)

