Fig 2 illustrates the conceptual framework of this programme. The intervention components of the programme target the individual and social environmental factors of the students to improve resilience and academic performance in students. Three levels of the student’s personal and social environment are defined:

Intrapersonal level: the first level represents the student’s own individual characteristics. The individual factors targeted by the programme are the student’s SEL competencies, behaviours and attitudes.Interpersonal level: the second level comprises relationships, culture, and society with whom the individual interacts. In the context of this programme, this level refers to factors in the student’s social network and primary support system in the school. In this level the programme targets change to the student’s networks and relationships with fellow students and teachers.Organisational level: the third level refers to factors influenced by the organisational system, in this context–the characteristics of the school. The programme targets change in attitudes and knowledge of teachers which will then translate into changes to the school characteristics, to result in a safe and supportive school climate, conducive for students’ growth and development.

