*Other covariates and factors for the testing of theory*. Other covariates and factors like the changes in the school climate and changes in relationships and social support network of the student will also be monitored. The Safe, Inclusive, and Respectful Climate survey [42] will be used to monitor teachers’ perceived changes in the school environment at the beginning, middle and end of the study. Changes in relationships and social support network will be elicited from periodic focus group discussions with teachers and documented qualitatively.

The relationship between SEL competencies, resilience and academic performance will also be tested.

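### In a single-arm, one-school study, path analysis can describe associations among student scores but cannot show that a mechanism carries a programme effect

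*Protocol article*

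**What the plan says.** Section 2.1 lists as a secondary question: "Do any of the proposed mechanisms in the conceptual framework explain the link between the programme, resilience and academic achievement". It adds whether the theory of change was realised. Table 1 numbers this as question 3 and assigns it the school climate survey, teacher focus groups, the Child Resilience Questionnaire, grades and the SSIS.

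On design, section 2.4 states: "A pre-post single arm design combined with qualitative and quantitative methods will be used to address the research questions". Section 2.6.1 describes one learning centre. Section 2.6.3 adds: "All students aged 6 to 19 still enrolled in the academic year of 2022 will be invited to participate". No comparison group is defined.

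On analysis, section 2.8.1 says that "path analysis will be used to test for mediators and moderators of SEL competencies and the relationship with resilience and academic performance in students". No other quantitative method is named for mediators.

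On measures, section 2.3 says: "Three levels of the student’s personal and social environment are defined". These are intrapersonal, interpersonal and organisational. Section 2.7.2 gives the intrapersonal level student scores (SSIS Social Skills and pre/post-tests). For the interpersonal level it says: "Changes in relationships and social support network will be elicited from periodic focus group discussions with teachers and documented qualitatively". The organisational level is followed by a teacher survey of school climate at the beginning, middle and end. For the outcome: "Academic achievement will be assessed using the Academic Performance subsection scores from the teacher report", with grade averages from school records as well.

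**The concern.** A mediation claim needs three things: a contrast in exposure to the programme, a mediator that responds to that contrast, and an outcome that responds to the mediator. Here the first is missing, because every student is in the programme arm. What can be estimated is whether students with better SEL competency also have better resilience or grades. That is a different question from the one in section 2.1.

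At stake is the conclusion drawn. Section 3 says the evidence will be used to plan expansion to other centres and to design a cluster randomised trial. A significant path reported under question 3 could be taken to mean that the theory of change was realised, when the data show only an association or a change over time.

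**Working it through.** **Inputs from the protocol.** One arm (2.4); one centre (2.6.1); all enrolled students aged 6 to 19 invited (2.6.3); 16 teachers at baseline (2.6.2); effect size 0.3, 80% power, 5% two-tailed, at least 90 students (2.6.3).

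**1. The plan's own figure.** For a paired mean change, the normal approximation is n = ((1.960 + 0.842)/0.3)² = 87.2, so 88. The exact paired t-test gives 89.1, so 90, with power 80.4% at 90. The stated 90 is therefore reproduced as a before/after mean-change figure. A correlation of 0.3 by Fisher z would give 85. Neither is a mediation calculation. I use n = 90 below.

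**2. Programme and climate as predictors across students.** At one wave, take four columns: intercept, programme (1 for everyone), school climate (one value for the school) and SEL score. The second and third columns are multiples of the first, so the matrix has rank 2 of 4. Neither a received-or-not programme indicator nor a whole-school climate value has a path that can be estimated across students, and adding students does not change this. Attaching each teacher's climate rating to a class would give at most 16 values, all rating the same school.

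**3. Before/after time standing in for the programme.** The path can then be computed, but it contains everything that changes with time. The check used 90 students, zero programme effect, the same drift in mediator and outcome (in SDs of change), correlation r between the two changes, and 4,000 runs per setting. The indirect path was declared when both legs were significant at two-sided 5%. Drift and r are my assumptions; the protocol gives neither.

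| Drift | r = 0.2 | r = 0.3 | r = 0.5 |
|---|---|---|---|
| 0 | 2.6% | 4.2% | 4.8% |
| 0.1 | 6.8% | 12.5% | 13.8% |
| 0.2 | 21.5% | 39.1% | 46.8% |
| 0.3 | 38.2% | 66.9% | 79.2% |
| 0.5 | 46.8% | 81.1% | 99.8% |

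Hand check: at drift 0.2 the time leg is significant in about 47% of runs, and a correlation of 0.2 in 90 students is significant in about 47%; 0.47 × 0.47 = 0.22, which agrees with 21.5%.

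**4. Framework levels with a separate student score.** Intrapersonal: yes. Interpersonal: teacher focus groups only. Organisational: teacher survey only. The Child Resilience Questionnaire does cover school and friends, but it is the resilience outcome, and using part of it as a mediator of resilience would be circular.

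**5. Informant.** Teachers are among the SSIS Social Skills informants and supply the SSIS academic score; section 2.8.1 does not say whose score enters the model. If a rater's general impression explains a share v of the variance of both scores, two otherwise unrelated scores correlate at √v × √v = v. By Fisher z with n = 90, power is about Φ(atanh(v)·√87 − 1.96):
- v = 0.10: about 15%
- v = 0.20: about 47%
- v = 0.30: about 82%

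The share v is an assumption with no source in the protocol, so these figures only show a range.

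**The case against.** The strongest reply is that the analysis sentence does not put the programme into the model. Read alone, and beside the statement in section 2.7.2 that the relation of SEL competencies to resilience and academic performance will be tested, it describes associations among student scores. Such an analysis can be run. This stands: the fault lies in the pairing with question 3, not in path analysis itself.

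Other parts of the reply also stand. Question 3 has a qualitative arm (Table 1), and sections 2.7 and 2.8.3 plan triangulation. The question is secondary, and the protocol warns of small numbers and limited time (2.6.3) and calls its evidence formative (section 3).

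A reader might also infer several stronger points that the document does not support:
- *That no exposure effect of any kind can be modelled.* Section 2.7.1 records attendance, duration and adherence, which can vary. They give a non-randomised contrast in intensity, and section 2.8.1 does not name them as exposures.
- *That climate and relationships are meant to enter a student-level path model.* Nothing says so; section 2.7.2 has climate monitored and relationships recorded qualitatively.
- *That two levels have no student-level information at all.* The school-and-friends content of the resilience questionnaire is student-level, and the circularity objection does not apply when the outcome is grades.
- *That the path model is bound to teacher ratings on both sides.* Student and parent SSIS forms and school-record grades are also collected.

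**Conclusion.** The concern holds in limited form. Question 3 asks about a programme effect, while the only quantitative mediation method named can deliver associations among student scores. The lack of a comparison group is sufficient for this conclusion and does not depend on sample size or on the simulation. Using before/after time as a stand-in gives a computable path that is confounded with time. With no programme effect, it was declared significant in 22% to 47% of runs at an assumed drift of 0.2 SD and in 38% to 79% at 0.3 SD (n = 90, assumed correlations 0.2 to 0.5). The interpersonal and organisational levels have no separate student-level measure. The same-rater problem is conditional and avoidable.

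This should be fixed before results are reported, but it does not touch the primary feasibility outcome. An analysis plan could narrow the claim; it could not supply the missing contrast.

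**What to change.** 1. In sections 2.1 and 2.8.1, restate the quantitative part of question 3 as exploratory: is within-student change in SEL competency associated with change in resilience or in grades, adjusted for baseline and age?
2. State that mediation of a programme effect is not tested in this study and is left to the cluster randomised trial announced in section 3.
3. Take the SEL score and the outcome from different informants already planned, for example student or parent SSIS with school-record grades, or parent SSIS with the student-reported resilience questionnaire. Table 1 gives teachers as the source of grades, so teacher-rated SSIS is the pairing to avoid there.
4. If an exposure is wanted, use recorded attendance and dosage, labelled non-randomised and exploratory.
5. Keep climate descriptive and relationships qualitative, as section 2.7.2 already implies.

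The cost is wording and analysis specification, with no new data. The downside is a more modest claim. Attendance is partly self-selected, so the result in item 4 stays exploratory.
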